# A nurse- and peer-led support program to assist women in gynaecological oncology receiving curative radiotherapy, the PeNTAGOn study (Peer and nurse support trial to assist women in gynaecological oncology): study protocol for a randomised controlled trial

**DOI:** 10.1186/1745-6215-14-39

**Published:** 2013-02-11

**Keywords:** Peer support, Nurse, Intervention, RCT, Gynaecological cancer, Radiotherapy, Distress, Quality of life, Psychosexual function

## Abstract

**Background:**

Women who undergo radiotherapy for gynaecological cancer (GC) can experience distressing side effects which impact on psychosocial functioning and intimate relationships. Cancer-related distress may be ameliorated by comprehensive preparation for treatment and addressing women’s informational, physical, psychological and psychosexual needs. This paper describes the protocol for a multisite randomised controlled trial (RCT) testing a novel intervention package which combines tailored specialist nursing consultations and telephone peer support with the primary aim to reduce psychological distress. Secondary aims assess patient quality of life, symptom distress, unmet supportive care needs, preparation for treatment, psychosexual functioning and vaginal stenosis.

**Methods/design:**

This multifaceted intervention comprises four nurse-led consultations coupled with four phone calls from a peer support volunteer (GC survivor). The evidence-based intervention will be delivered at critical points in the illness trajectory: pre-treatment, mid-treatment, treatment completion and post-treatment. Nurses and peers undergo 2-day intensive training workshops, are guided by comprehensive study intervention manuals and receive ongoing supervision and support. Eligible patients will have a diagnosis of GC, be scheduled to receive curative radiotherapy, be aged 18 years or over and speak English. Three-hundred and six participants will be randomized to receive usual care or usual care with the intervention package. Study outcome measures will be collected at baseline, day 1 of radiotherapy and 1, 6 and 12 months post radiotherapy. Clinical assessments of vaginal toxicity will occur at baseline, and 3, 6, and 12 months post radiotherapy.

**Discussion:**

This timely research has the potential to substantially reduce the physical, psychosexual and supportive care needs of women with GC. Using a telephone peer support model, the intervention package ensures equitable access to support services for geographically isolated patients. The novel intervention engages peer volunteers who liaise with nurses to encourage adherence to professionally-delivered information and provide emotional support. It has been designed to be potentially transferable to a range of treatment settings and diseases. Based on pilot data, the proposed intervention was found to be useful and acceptable to patients and clinicians. If effective and feasible in the multisite RCT, the program could be widely disseminated.

**Trial registration:**

Australian New Zealand Clinical Trial Registry ACTRN12611000744954

## Background

### Physical and psychological burden of disease

Gynaecological cancers (GC) account for 19% of all female cancers worldwide
[1], and in addition to the psychological implications of living with cancer, women with GC experience significant psychosexual and psychosocial issues unique to their diagnosis
[2,3]. A common treatment for GC is radiotherapy, which can cause many distressing side effects that have both immediate and late impacts on quality of life (QoL)
[4]. These side effects include diarrhoea
[5], abdominal cramps
[5], bladder dysfunction
[6], menopause, infertility
[6] and sexual dysfunction
[6]. Women may also experience vaginal side effects including stenosis, atrophy, agglutination, reduced genital sensation, vaginal dryness, dyspareunia and postcoital bleeding
[2,7]. As these side effects involve intimate and private aspects of bodily function their presence also has a major impact on close relationships and social functioning.

Not surprisingly, upwards of 40% of GC patients report chronic and distressing sexual difficulties
[2], which may continue over the 12 months post treatment
[8]. GC diagnosis also commonly impacts upon a woman’s self-esteem, body image, femininity and intimate relationships
[2,3]. Yet up to half of GC patients report not having any discussions with their clinicians about post-treatment sexual adjustment
[8,9], which represents a concerning gap in the provision of healthcare.

In addition to the physical impact, over half of patients with cancer feel anxious prior to treatment and about 40% remain anxious at treatment completion
[3]. High anxiety has been associated with poorer sexual functioning
[8], worse QoL up to 1 year post treatment
[10] and lower social support among women with GC
[11]. However, anxiety levels may be ameliorated by both comprehensive preparation for treatment and addressing needs during treatment
[12,13].

A Cochrane review published in 2008 recommends women use a vaginal dilator and/or engage in regular sexual intercourse
[7] to minimise vaginal stenosis and agglutination after pelvic radiotherapy for GC. Patient adherence to such strategies is associated with less physical damage and greater sexual satisfaction
[7,14], and allows adequate pelvic examination to detect cancer recurrence
[15]. However, adherence is suboptimal
[7,8]. Moreover, a more recent Cochrane review generated debate over the appropriate use of dilators by concluding that there was insufficient data to recommend routine use
[16]. While recommended practice varies across treatment centres
[15], current practice guidelines internationally advocate the use of a vaginal dilator for women receiving pelvic radiotherapy
[17-20].

### Innovative, evidence-based model of supportive care

Given the physical and psychological impact of GC, there is a high need to provide appropriate and timely interventions to women with these cancers. An evidence-based intervention combining nurse-led consultations with peer telephone support has the potential to address these needs.

Level 1 evidence shows that providing sensory and procedural information, and addressing patients’ fears about surgery results in less pain, distress and fewer days in hospital
[12,13]. Only two studies have applied these principles to the radiotherapy context; one found provision of sensory and procedural information about radiotherapy resulted in reduced anxiety
[21]; the other, a RCT involving taped procedural and coping information, resulted in increased perceived knowledge and self-efficacy
[22]. This high level evidence has been incorporated into the study design as a radiotherapy area tour.

A systematic review showed that there are effective, evidence-based self-care strategies for side effects common to several cancer treatments such as fatigue, diarrhoea and infertility
[23]. In addition, involving patients with chronic disease in their disease management results in improved self-reported health and lower psychological distress, less health system use and reduced health costs
[24,25]. It is therefore likely that women treated for GC with radiotherapy would benefit from a coordinated provision of individualised, evidence-based interventions and resources to optimise their recovery.

Nurse-led consultations and telephone interventions for cancer patients have been shown to be appropriate and effective
[26]. Of interest, health professional delivery of tailored information to women with GC about side effects and effective self-care has been linked to better coping with side effects; compliance with post-radiation rehabilitation; less fear about sexual intercourse and less relationship disruption
[14,27]. In addition, evidence from a RCT shows that nurse coordinated multidisciplinary and community referrals result in better symptom control for cancer patients
[28]. Aranda and colleagues have recently demonstrated that a nurse-led pre-chemotherapy educational consultation was effective in reducing pre-treatment anxiety amongst those experiencing moderate to high anxiety at baseline
[29]. As such, individualised and targeted nursing consultations with provision of evidence-based self-care strategies are an integral component of the intervention design.

Multidisciplinary care (MDC) refers to a team approach to healthcare delivery that involves input from all relevant medical, nursing and allied health areas. MDC has been linked to a number of improvements in disease outcomes, including survival benefits and better QoL, lower distress, decreased length of hospital stay, reduction in healthcare costs, improved staff satisfaction and improved knowledge of patient care
[3,27,30]. No studies testing a system to facilitate MDC for women with GC have been identified. Effective referral requires that clinicians have excellent communication skills to elicit and respond to patient emotional and information cues. A systematic review showed that communication skills training programs improve clinicians’ skills and confidence in psychological assessment and interviewing
[31]. The intervention includes training of study nurses to facilitate appropriate, timely and effective MDC referrals.

In addition to nursing interventions, models of psychosocial cancer care have identified a pivotal role for peer-support programs
[32]. The unique perspective of a peer facilitates sharing and practical, social and emotional coping
[33,34]. A systematic review of cancer peer-support programs indicated high satisfaction and perceived psychosocial benefits among participants
[33]. Some patients even prefer peer-delivered over professionally-delivered support
[35]. Telephone models of peer support have additional economic and logistic advantages, and are successful in reaching housebound or geographically isolated patients
[36].

Despite widespread use and positive participant perceptions
[33], only two RCTs testing one-to-one telephone peer support have been identified in the cancer literature
[37,38]. Rudy and colleagues found that perceived social support was higher among melanoma patients receiving telephone peer support
[38]. The second study reported no significant difference in newly diagnosed GC patient’s emotional distress with peer telephone support, however the sample size was small (*n*=32)
[37]. No RCTs investigating peer-support interventions from treatment initiation to post-treatment completion were identified
[33,35], and none have been found that combine tailored nurse consultations with telephone peer support.

This study will evaluate the effect of an innovative, nurse-led intervention combined with telephone-based peer support to provide evidence-based information and resources, coaching in self-care, multidisciplinary referrals and psychological support to optimise the recovery of women treated for GC with radiotherapy.

### Study aims

The primary aim is to evaluate the effectiveness of the intervention package to reduce psychological distress for women receiving radiotherapy with curative intent for GC. Secondary aims are to examine the impact of the intervention on patient quality of life, symptom distress, unmet supportive care needs, preparation for treatment, psychosexual functioning and vaginal stenosis.

### Study hypotheses

#### Primary endpoint

Compared to the usual care group, the intervention group will report lower psychological distress from baseline to first follow-up immediately prior to the first radiotherapy treatment, and follow-up at 4 weeks post treatment.

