### Sample size

The treatment effect is conservatively estimated to result in group differences of 0.35 standard deviations for continuous outcome measures
[45-47]. With the Hospital Anxiety and Depression Scale total score (HADS-T) as the primary outcome, to achieve ≥80% power at a 5% significance level, the required sample size in each arm is 130 at the 12-month follow-up. With a patient approach rate estimated at 85%, consent rate estimated at 60% and attrition estimated at 15%, 600 participants will need to be approached to achieve a sample of 260.

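### The primary hypothesis covers distress at two early visits, but the stated power and significance level belong to one comparison placed at 12 months, and no rule says what decides the trial

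*Protocol article*

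**What the plan says.** In the protocol article, the Primary endpoint paragraph under Study hypotheses expects the intervention group to have "lower psychological distress from baseline to first follow-up immediately prior to the first radiotherapy treatment, and follow-up at 4 weeks post treatment". Table 1 calls these visits Follow-up 1 (FU1) and Follow-up 2 (FU2).

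The Sample size section confirms the measure: "With the Hospital Anxiety and Depression Scale total score (HADS-T) as the primary outcome". It assumes "group differences of 0.35 standard deviations for continuous outcome measures" and then states that "to achieve ≥80% power at a 5% significance level, the required sample size in each arm is 130 at the 12-month follow-up". Twelve months is Follow-up 4. HADS is collected there, but neither the primary hypothesis nor any secondary one concerns distress at 12 months. Only psychosexual functioning and vaginal stenosis have 12-month hypotheses.

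The Outcome analysis section fits one linear mixed model per outcome, with polynomial time, group, site and interactions, and names no decisive contrast or visit. The Secondary descriptive section ties between-group changes to the follow-ups in the hypotheses, but only descriptively. The opening of Statistical analyses allows every method to be reviewed, and revised if need be, once the data have been inspected.

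On recruitment, the same sample-size paragraph gives an approach rate of 85%, a consent rate of 60% and "attrition estimated at 15%, 600 participants will need to be approached to achieve a sample of 260". The Abstract says "Three-hundred and six participants will be randomized".

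**The concern.** A power statement describes one test. Here the endpoint paragraph points to two visits and the sample-size paragraph to a third, and nothing links them. The word joining the two visits in the hypothesis could mean that both must show a difference, that each is a separate chance of success, or that the effect is judged over the two together. These rules have different error rates and different power at the same sample size, so the stated 5% and 80% cannot be assigned to the primary endpoint as written.

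What is at stake is freedom after the fact. With no rule fixed, and with methods open to revision after data inspection, the choice between FU1, FU2 and a combination could be made once the results are visible.

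**Working it through.** **Inputs from the protocol.** Effect 0.35 SD, 5% level (two-sided reproduces the plan's figure), 130 per arm, 15% attrition (Sample size); 306 randomised, so 153 per arm at 1:1 (Abstract; Study integrity).

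**Assumed, because the protocol does not give it.** The correlation ρ between the FU1 and FU2 treatment comparisons is 0.4 to 0.7, with 0 to 0.9 as an outer range. The effect is 0.35 SD at both visits, with no baseline adjustment.

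**1. The plan's own figure.** n per arm = 2(1.960 + 0.842)² / 0.35² = 128.1, so 129 by the normal approximation. The exact t-test gives 79.97% power at 129 and 80.3% at 130. So 130 per arm is correct for one two-sided comparison at one visit. Also 260 / 0.85 = 305.9, so 306 randomised.

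**2. Does the 12-month label cost power?** If 130 per arm remain at 12 months, at least as many should be available earlier. By the normal approximation, one comparison at an earlier visit has 80.6% power at 130 per arm and 86.5% at 153. The label alone therefore loses nothing.

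**3. Three rules for two visits.** Each visit's z-statistic has mean 0.35 × √(n/2), which is 2.82 at 130 per arm and 3.06 at 153. The two statistics are taken as bivariate normal with correlation ρ.

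- *Either visit, unadjusted:* P(|z₁| > 1.96 or |z₂| > 1.96) under no effect.
- *Both visits:* P(z₁ > 1.96 and z₂ > 1.96) under 0.35 SD at each.
- *One averaged contrast:* the mean of the z-statistic becomes 2.82 / √((1+ρ)/2), with one test at 5%. At ρ = 0.4 this is 2.82 / 0.837 = 3.37, power Φ(3.37 − 1.96) = 92%. At ρ = 0.7 it is 2.82 / 0.922 = 3.06, power Φ(3.06 − 1.96) = 86%.

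| ρ | Either: type I error | Both: power at 130 | Both: power at 153 | Averaged: power at 130 (type I 5%) |
|---|---|---|---|---|
| 0.4 | 9.3% | 68.4% | 77.1% | 92.1% |
| 0.5 | 9.1% | 69.5% | 77.9% | 90.3% |
| 0.6 | 8.8% | 70.7% | 78.8% | 88.4% |
| 0.7 | 8.3% | 72.0% | 79.8% | 86.5% |

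Over ρ from 0 to 0.9, the either-visit error runs from 9.75% down to 7.0%. Power for both visits runs from 64.9% to 75.6% at 130 per arm and from 74.8% to 82.6% at 153.

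**4. Sensitivity to baseline adjustment.** Let r be a common correlation among baseline, FU1 and FU2. Adjusting for baseline divides the mean z by √(1 − r²) and leaves a correlation of r/(1 + r) between the visits. Power for both at 130 per arm is then 77% (r = 0.4) to 96% (r = 0.7). With change scores the divisor is √(2(1 − r)) and the correlation is 0.5, giving 60% to 92%.

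**5. Recruitment chain.** 600 × 0.85 = 510; 510 × 0.60 = 306; 306 × 0.85 = 260.1. The totals agree only if 600 are eligible and 510 approached. If 600 were approached, 600 × 0.60 = 360 would be randomised and 360 × 0.85 = 306 retained, against the stated 306 and 260.

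**The case against.** The strongest reply is that an article condenses the plan, and that contrasts and multiplicity rules usually stand in the full protocol or SAP. That is fair for the detail of the contrast. It does not remove the disagreement inside this document, where the endpoint paragraph and the sample-size paragraph name different time points.

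A second reply is that the 12-month figure is a retention floor. That reading is reasonable, and it disposes of the idea that the label itself lowers power.

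A third is that the mixed model can supply one overall test. It can, and a contrast averaged over FU1 and FU2 would more than meet the stated power. But the model covers four follow-ups, and the protocol does not single out that contrast.

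Three stronger readings are tempting and not supported:

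- *The stated error rate or power fails whichever rule is used.* The averaged contrast keeps 5% and exceeds 80%.
- *Power is well below 80%.* That needs the both-visits rule, 130 per arm already at the early visits and no baseline adjustment. The hypothesis speaks of change from baseline and HADS is measured there, so step 4 matters. With 153 per arm the shortfall is already small.
- *The trial could be called positive on 12-month distress.* No distress hypothesis names 12 months.

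**Conclusion.** The point holds as a conflict over which test the trial is designed around. The arithmetic behind 130 per arm and 306 randomised is right, but it describes a single comparison, placed at a visit outside the primary hypothesis. Whether 5% and 80% apply to the primary endpoint depends on a rule that the protocol does not state.

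Under the stated assumptions, an unadjusted either-visit rule breaks the 5% level, a both-visits rule falls short of 80% at 130 per arm, and an averaged contrast satisfies both. The both-visits figure is the most fragile because it moves with the numbers retained and with baseline adjustment. The type I error of the either-visit rule does not depend on sample size.

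This should be fixed, because it concerns what counts as success. It is not evidence of an underpowered trial. The recruitment wording is a minor slip with no effect on error rates or sample size.

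**What to change.** Before any look at outcome data, state one primary test in the Primary endpoint paragraph:

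- a single mixed-model contrast of the group difference in HADS-T averaged over FU1 and FU2, at 5%; or
- one named visit at 5%, followed by the other at 5% only if the first succeeds. FU2 first is one option, since Table 1 marks it as post intervention. FU1 first is also arguable, since the description of intervention session 1 says that anxiety is typically highest just before treatment.

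If both visits must succeed, say so and restate the power for that rule, with its assumed correlation and any baseline adjustment.

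Then base the sample-size sentence on the chosen test: 130 per arm evaluable at the primary visit or visits, with the 15% loss by 12 months as a conservative allowance.

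In the same paragraph, correct the recruitment wording to 600 eligible, 510 approached, 306 randomised and 260 retained.

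The cost is a change of wording and no extra patients for either listed test. If both visits must succeed and 80% is to be kept without baseline adjustment, 160 evaluable per arm would be needed at ρ = 0.5 and 154 at ρ = 0.7. The downside is that one visit alone can no longer carry the trial after the fact. The averaged contrast also dilutes an effect present at one visit only: 0.35 SD at one and none at the other averages to 0.175 SD.

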#### Secondary endpoints

Compared to the usual care group, the intervention group will report:

1. Lower informational and psychosocial supportive care needs and lower symptom distress from baseline to follow-up at 4 weeks post treatment,

2. Better preparation for treatment from first follow-up immediately prior to the first radiotherapy treatment to follow-up at 4 weeks post treatment,

3. Higher psychosexual functioning from baseline to follow-up at 6 and 12 months post treatment,

4. Higher quality of life from baseline to follow-up at 4 weeks post treatment, and

5. Less vaginal stenosis at 3, 6 and 12 months post treatment.

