##### Intervention session 1: pre-treatment, face-to-face, 1 hour

Patients with cancer often report increased unmet needs related to the worries and fears of family members
[39], so women will be encouraged to bring a significant other to the consultation. Given that anxiety related to treatment is typically highest just prior to starting treatment
[3] and based on Level I evidence on treatment preparation
[12,13] each patient will be given a brief tour of the treatment unit followed by a private consultation. The nurse will first ascertain the patient’s understanding of their situation and clarify misconceptions. A radiotherapy question prompt sheet developed from the literature and with consumer and professional input will be administered by the nurse and at the first three sessions to guide tailoring of the intervention. The patient identifies her top three concerns for focus in the session, with further concerns addressed at future sessions. The prompt sheet also assesses global distress using the Distress Thermometer
[40]. Anxious patients will be trained to use the strategy of controlled breathing with positive self-talk, an effective self-care activity to reduce treatment-related anxiety
[41]. The prompt sheet will aid a discussion of the woman’s supportive care needs and possible MDC referrals. The nurse will discuss vaginal health, psychosexual rehabilitation, and if appropriate, menopause and infertility. Coaching and rehearsal of self-care for side effects and stress-reduction will be offered, and tailored fact-sheets and information provided which can improve recall
[30]. At the end of each session the nurse arranges a time for a call with the peer volunteer. The nurse also confirms any particular concerns the patient does not wish to discuss with her peer.

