### Measures

Patients will complete self-report, pen and paper measures. Clinical vaginal assessments will be completed by the treating clinician. Table 
1 presents when measures will be administered.

**Table 1 T1:** Time-points for collection of patient reported outcomes and clinical outcomes for the PeNTAGOn study

**Time-point**	**Questionnaire**
Baseline & clinical exam I: (pre-treatment)	Demographic and clinical variables, HADS, FACT-G, SCNS-SF34-R, MSAS-SF, SVQ, clinical exam I (LENT SOMA scale)
Follow-up 1: (immediately prior to first radiotherapy)	HADS, CaTS
Follow-up 2: (4 weeks post radiotherapy and post intervention)	HADS, FACT-G, SCNS-SF34-R, MSAS-SF, AQ, CaTS and Patient Care evaluation & Referrals
Clinical exam II (3 months post radiotherapy)	Clinical exam II (LENT SOMA scale)
Follow-up 3 & clinical exam III: (6 months post radiotherapy)	HADS, FACT-G, AQ, SVQ, clinical exam III (LENT SOMA scale)
Follow-up 4 & clinical exam IV: (12 months post radiotherapy)	HADS, FACT-G, AQ, SVQ, clinical exam IV (LENT SOMA scale)

AQ, Adherence questionnaire; CaTS, Cancer Treatment Survey; FACT-G, Functional Assessment for Cancer Therapy - General; HADS, Hospital Anxiety and Depression Scale; LENT SOMA, Late Effects of Normal Tissues / Subjective-Objective Management Analytic; MSAS-SF, Memorial Symptom Assessment Scale Short Form; SCNS-SF34-R, Supportive Care Needs Survey - short form, Revised response format; SVQ, Sexual function-vaginal changes questionnaire.

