#### Cancer treatment-related information and support needs

Schofield *et al*. developed a 25-item Cancer Treatment Survey (CaTS)
[69] which comprises two subscales for specific information and support needs domains: sensory-psychological concerns and procedural concerns. Both subscales have demonstrated high internal consistency (alpha>0.90) and good divergent validity (with HADS: r<0.26)
[69]. Both were sensitive to change in a recent RCT
[29].

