#### Secondary descriptive and planned subgroup analysis

For descriptive purposes, observed data will be used to calculate within- and between-groups changes in study outcomes from first assessment to follow-ups as specified in the study hypotheses. Effect sizes for between-groups differences will be calculated using recommended procedures
[71]. Interpretation of changes in the primary outcome will be facilitated by results from an analysis of participants’ global ratings of change in psychological distress
[72,73]. For the primary outcome, subgroup analysis will be used to investigate whether the intervention effect differs significantly between participants with and without clinically significant distress at baseline.

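### Secondary hypothesis 2 takes preparation for treatment from Follow-up 1, after the preparation session, so a change contrast drops any benefit already reached

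*Protocol article*

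**What the plan says.** Secondary endpoints, item 2, predicts for the intervention arm "Better preparation for treatment from first follow-up immediately prior to the first radiotherapy treatment to follow-up at 4 weeks post treatment".

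The instrument is the CaTS, which "comprises two subscales for specific information and support needs domains: sensory-psychological concerns and procedural concerns". In Table 1 (Measures) the baseline row reads "Demographic and clinical variables, HADS, FACT-G, SCNS-SF34-R, MSAS-SF, SVQ, clinical exam I (LENT SOMA scale" and has no CaTS. The CaTS appears with the HADS at FU1, immediately before the first radiotherapy, and again at FU2, four weeks after radiotherapy, in the set "HADS, FACT-G, SCNS-SF34-R, MSAS-SF, AQ, CaTS and Patient Care evaluation & Referrals".

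The preparation work is in "Intervention session 1: pre-treatment, face-to-face, 1 hour", where "each patient will be given a brief tour of the treatment unit followed by a private consultation". The primary hypothesis expects an effect by FU1: "lower psychological distress from baseline to first follow-up immediately prior to the first radiotherapy treatment".

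Two passages bear on the analysis. Outcome analysis fits a linear mixed model to each outcome, with fixed effects for time, group and site and their interactions. Secondary descriptive and planned subgroup analysis adds, for description, between-group "changes in study outcomes from first assessment to follow-ups as specified in the study hypotheses".

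**The concern.** For CaTS the first assessment is FU1, and FU1 follows the session designed to improve what CaTS measures. Items 1, 3 and 4 use the same from-to wording but start from a true pre-intervention baseline. In item 2 a post-intervention value takes that place.

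If item 2 is tested as written, as a change from FU1 to FU2, the benefit of the preparation session sits in the starting level and is subtracted out. Preparation for treatment is a named secondary aim, so a session that worked could be reported as having had no effect.

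**Working it through.** **1. What the wording fixes.** Item 5 is phrased as a level at stated times; item 2 is phrased from one time to another, like items 1, 3 and 4. The descriptive section speaks of first assessment rather than baseline. By Table 1, CaTS is the only outcome named in the hypotheses whose first assessment is not baseline. Together these favour reading item 2 as a change from FU1.

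**2. The plan's own figure.** Sample size assumes 0.35 SD, a 5% level (taken as two-sided) and at least 80% power.
- n per arm = 2 × (1.960 + 0.842)² / 0.35² = 128.2, rounded up to 129. The t-test version gives 129.1, so 130, which matches the protocol.
- Power with 130 per arm is 80.6% (t-test 80.3%).
- 600 × 0.85 × 0.60 = 306 randomised, and 306 × 0.85 = 260.

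The sample size reproduces and is not in dispute.

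**3. The change contrast.** Let d1 and d2 be the between-arm benefits at FU1 and FU2 in SD units, positive when the intervention is better, and let ρ be the within-woman correlation of CaTS between the two times.
- Expected contrast = d2 - d1
- SD of a change = √(2(1 - ρ))
- Standard error = √(2(1 - ρ)) × √(2/130)

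The protocol gives neither separate effects at the two times nor ρ. Assumed: d1 = 0.35, d2 from 0 to 0.70, ρ = 0.3, 0.5, 0.7. Example with d2 = 0.20 and ρ = 0.5: the SD of change is 1, the standard error is 0.124, and z = -0.15 / 0.124 = -1.21. The chance of significance against the intervention is Φ(1.21 - 1.96) = 22.6%.

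| d2 | Contrast (SD) | Significant for (ρ = 0.3 / 0.5 / 0.7) | Significant against (ρ = 0.3 / 0.5 / 0.7) | Estimate below zero (ρ = 0.3 / 0.5 / 0.7) |
|---|---|---|---|---|
| 0.70 | +0.35 | 66.5 / 80.6 / 95.4% | about 0% | 0.9 / 0.2 / 0.0% |
| 0.50 | +0.15 | 17.4 / 22.6 / 34.5% | at most 0.1% | 15.3 / 11.3 / 5.9% |
| 0.35 | 0 | 2.5% | 2.5% | 50% |
| 0.20 | -0.15 | at most 0.1% | 17.4 / 22.6 / 34.5% | 84.7 / 88.7 / 94.1% |
| 0.10 | -0.25 | about 0% | 39.9 / 52.2 / 74.0% | 95.6 / 97.8 / 99.5% |
| 0 | -0.35 | about 0% | 66.5 / 80.6 / 95.4% | 99.1 / 99.8 / 100.0% |

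**4. The level comparison at FU1.** With d1 = 0.35 the standard error is √(2/130) = 0.124, and power is 80.6% whatever happens after FU1. With all 306 / 2 = 153 per arm it is 86.5%.

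**The case against.** Four points on the other side have weight.

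- The change calculation in the protocol is expressly descriptive; it does not set the test of any hypothesis. This stands.
- The mixed model contains a group term. With time zero at FU1 and the interaction in the model, that term can give the between-arm CaTS difference at FU1. Which coefficient answers which hypothesis may be settled in an analysis plan that is not shown. This also stands: the model can deliver the right quantity. But the hypothesis wording, which is shown, points away from it, and nothing links item 2 to the group term.
- Item 2 promises better preparation, not greater improvement, and could be read as a level held over the period. That reading is possible, but the parallel items and the descriptive section make it the weaker one.
- Sessions 2 to 4, and possibly the first peer call (a week after session 1), fall after FU1. Any benefit they add stays in the contrast. If the whole effect arose after FU1 (d1 = 0, d2 = 0.35), nothing would be lost.

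A reader might infer something stronger: that the analysis will come out with the wrong sign because usual-care women catch up by going through treatment. The documents do not support that. They nowhere state such convergence, and the sign depends on it. A reader might also infer that the effect is removed entirely; only the part reached by FU1 is.

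**Conclusion.** The point holds for the contrast that item 2 describes. CaTS has no pre-intervention value, session 1 precedes FU1, and a change from FU1 (or the group-by-time term alone) cannot credit benefit already present at FU1. A benefit held equally at both times has an expected contrast of zero, and this needs no assumption about catch-up. A benefit that shrinks gives a negative contrast. Only benefit added after FU1 shows the right sign; from 0.35 SD it would have to double to 0.70 SD to give 67% to 95% power. These sizes rest on assumed effects and on correlations of 0.3 to 0.7.

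Severity is moderate. One secondary hypothesis is affected. The primary endpoint uses the HADS, which has a true baseline, and the sample size is untouched.

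**What to change.** - Restate item 2 as the between-arm difference in CaTS level at FU1, with the difference in level at FU2 as supporting.
- Estimate both from the planned mixed model, adjusted for treating hospital and treatment type (the stratification factors under Study integrity), and name the contrast that answers item 2.
- Do not use the FU1-to-FU2 change, or the group-by-time term, as the test of this hypothesis.
- If CaTS change is still reported descriptively, label it as change after the first intervention session.

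Randomisation makes the level comparison valid without a baseline CaTS. The cost is wording only, with no new data or assessments. Recruitment is open, so the change should be recorded before any outcome analysis, so that the contrast is not seen as chosen after the data were known.
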